#### Immediate blood test ordering

GPs from group 1 are instructed to order blood tests immediately when including a patient in the study. The GPs are free to decide on the number and type of blood tests. The patient takes the blood test ordering form to the regional laboratory participating in the study. At the laboratory, the tests ordered by the GP are supplemented by the complaint-specific tests from the sets described in table 1. Only results of tests ordered by the GPs themselves are fed back. If a GP does not intend to order any tests (but is obliged to do so by the study protocol), the results of the four tests recommended by the NHG guideline are fed back, because patients expect results after a blood sample has been taken.

#### Watchful waiting for 4 weeks

GPs from groups 2 and 3 propose to the patients they include to observe a 4-week watchful waiting policy. When watchful waiting is not considered feasible by the GP, e.g. because a patient insists on being tested, test ordering is allowed. In that case, the GPs are asked to state the reasons for not postponing test ordering on a special form.

#### Reference standard

The nature of unexplained complaints implies that no proper gold standard exists. Hence, we opted for a delayed type cross-sectional study design.[21,22] In this type of design, the diagnosis after the 12-month follow-up period is used as a reference standard. This diagnosis is established separately by two researchers, making use of information from the GPs' patient records. Differences are discussed and consensus is sought. If consensus cannot be reached, the case is presented to an expert panel that takes the final decision. No restrictions are imposed on GPs as to patient management during follow-up.

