### Blinding

#### Researchers

The researchers are not blinded for the trial group allocation of the participating GPs. They are not involved in the GPs' decision to label patients as having unexplained complaints, nor in the test ordering procedure or the reporting of the results of the laboratory tests.

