#### Patients

Findings of history taking and physical examination are recorded on a prestructured complaint registration form by the GP after the consultation(s).

All patients are given the first questionnaire at the first consultation and a second questionnaire at the second consultation after 4 weeks. Patients who do not return to their GP after 4 weeks are sent a questionnaire by mail. Patients from all groups receive follow-up questionnaires by mail at 6 and 12 months after the initial consultation.

After 12 months, i.e. at the end of the follow-up period, data on the final diagnosis and health care consumption are collected from the patients' records by the researchers (MB and HK).

Copies of test ordering and result forms are collected by the researchers (MB and HK) from the regional laboratories.

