### Data analysis

#### Primary outcome measures of the diagnostic intervention

The first primary outcome is the accuracy and added value of blood tests in detecting serious pathology (per test and in combinations relevant to general practice), related to and in addition to signs and symptoms. Serious pathology is defined as pathology requiring treatment. The second primary outcome is the effect of a 4-week postponement of test ordering on the blood test characteristics.

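### The reference diagnosis is set by unblinded researchers with access to the index test results, which puts the accuracy estimates at risk of review bias and, for fed-back tests, incorporation bias

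*Protocol article*

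**What the plan says.** - **Who sets the diagnosis, and from what (Reference standard).** "This diagnosis is established separately by two researchers, making use of information from" the GP's notes. Disagreements go to consensus and then to an expert panel. On the work-up that feeds those records: "No restrictions are imposed on GPs as to patient management during follow-up".
- **Blinding (Blinding, Researchers).** "The researchers are not blinded for the trial group allocation of the participating GPs". They are kept out of labelling complaints as unexplained, "nor in the test ordering procedure or the reporting of the results of the laboratory tests".
- **Data collection (Measurements, Patients).** At 12 months "data on the final diagnosis and health care consumption are collected from the patients' records by the researchers", and "Copies of test ordering and result forms are collected by the researchers" from the regional laboratories. Both sentences identify the same two people.
- **What the GP sees (Blinding, GPs; Immediate blood test ordering).** The GP receives the results of tests he or she ordered, or of the four guideline tests if none was intended. Results of the supplementary complaint-specific tests are withheld.
- **Target condition (Primary outcome measures of the diagnostic intervention).** "Serious pathology is defined as pathology requiring treatment". The two primary outcomes there are the accuracy and added value of the tests, and the effect of a 4-week postponement on test characteristics.

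**The concern.** In an accuracy study the reference diagnosis should be reached without knowledge of the index test. Here there are two routes by which the test can influence it.

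1. **Review bias, for all tests.** The researchers who hold the laboratory forms, including the withheld supplementary results, appear to be the ones who assign the diagnosis. Whether a condition requires treatment is a judgement, and an abnormal value in hand can tip it.
2. **Incorporation bias, for fed-back tests.** A result returned to the GP can be written in the notes and prompt further work-up, and the notes are the source of the diagnosis.

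Two separate readings, consensus and a panel improve agreement. They do not remove a bias that all readers share. Because both diagnostic primary outcomes rest on this diagnosis, the tests could look more useful than they are. Pathology is rare in this setting, so false positives greatly outnumber cases and a small amount of relabelling goes a long way.

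**Working it through.** **Inputs from the article (Power calculation).** Prevalence of serious pathology 2%; 100 cases wanted. The stated size reproduces: 100 / 0.02 = 5000 patients, about 1667 per group.

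**Inputs assumed, not in the article.** True sensitivity 0.60 and specificity 0.90 for a single test. A share f of false positives is labelled as pathology because of the positive result, with f = 2%, 5% or 10%. For simplicity all 5000 patients are treated as tested.

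**Starting table.** True positives 0.60 × 100 = 60; false negatives 40. False positives 0.10 × 4900 = 490; true negatives 4410. True PPV = 60 / 550 = 0.109.

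**After relabelling.** With r = f × 490:
- apparent sensitivity = (60 + r) / (100 + r)
- apparent PPV = (60 + r) / 550
- apparent specificity = 4410 / (4900 − r)

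| f | r | Sensitivity | PPV | Specificity |
|---|---|---|---|---|
| 0 | 0 | 0.600 | 0.109 | 0.900 |
| 2% | 9.8 | 69.8/109.8 = 0.636 | 0.127 | 0.902 |
| 5% | 24.5 | 84.5/124.5 = 0.679 | 0.154 | 0.905 |
| 10% | 49 | 109/149 = 0.732 | 0.198 | 0.909 |

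If 10-25% of the false negatives are also labelled as no pathology because the result was normal, sensitivity becomes 0.66-0.70, 0.70-0.74 and 0.75-0.78 for the three values of f.

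**Range over other assumptions** (f from 2% to 10%, false negatives left alone):
- True sensitivity 0.40: apparent 0.45-0.60 at specificity 0.90, and 0.43-0.52 at specificity 0.95.
- True sensitivity 0.80: apparent 0.82-0.87 and 0.81-0.84 respectively.

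The direction is the same throughout.

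**Does the bias differ by arm?** Take f = 5% and the same true accuracy in all tested patients.
- Group 1, all tested at T0: 1667 patients, 33.3 cases, 20 true positives, 163.3 false positives, r = 8.17. Apparent sensitivity (20 + 8.17) / (33.3 + 8.17) = 0.68.
- Groups 2 and 3 (3333 patients, 66.7 cases, 3266.7 non-cases), if every case returns for testing. With 20% of non-cases returning, r = 0.05 × 0.10 × 653.3 = 3.27 and sensitivity is (40 + 3.27) / (66.7 + 3.27) = 0.62. With 50% returning, r = 8.17 and sensitivity is 48.17 / 74.83 = 0.64.
- Groups 2 and 3, if cases and non-cases return in the same proportion: false positives per case are as in group 1, and the result is again 0.68.
- Groups 2 and 3, if 40% of cases and 50% of non-cases return: 26.7 cases, 16 true positives, r = 8.17, giving 24.17 / 34.83 = 0.69.

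The difference between arms therefore depends on who returns, which the article does not give. It also depends on f being equal across arms, which is a further assumption.

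**The case against.** The defence has several good points.

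- **Access is not use.** The article says the diagnosis is set from GP records. It does not say the laboratory forms are consulted, and that the two assessors are the two collectors is likely but inferred. This stands: the text shows a risk, not a bias that has occurred.
- **The article condenses a fuller protocol.** Silence on masking to index results could be an omission in the article. However, its Blinding section covers researchers expressly and says they know the allocation. Keeping them out of ordering and reporting is not masking when the diagnosis is set.
- **Supplementary results are withheld from GPs.** This is real protection. Incorporation through the record applies only to fed-back tests; for withheld tests the only route is the forms the researchers hold.
- **The design was chosen deliberately.** No gold standard exists, and effects of results on treatment are themselves outcomes. That justifies using follow-up and leaving GPs partly unblinded. It does not require the diagnosis assessors to know arm or results.
- **A diagnosis prompted by a blood test can be true.** Correct. Glucose, TSH or haemoglobin may be the evidence that establishes the condition, so not every such diagnosis is an artefact.

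A reader might also infer that the group 1 versus groups 2 and 3 comparison is biased towards immediate testing. The documents do not establish this. Untested patients contribute no index result, returning patients in groups 2 and 3 are tested, and the feedback rule in the blinding section is stated for all GPs. More false positives per case in unselected group 1 testing makes excess bias there plausible, but it rests on assumed return rates.

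**Conclusion.** The concern holds as a risk of bias. The researchers are stated to know the arm, the collectors of the final diagnosis also hold the index results, and no step of the diagnostic process, including the panel, is described as masked. Both diagnostic primary outcomes are exposed.

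The expected effect is inflation of sensitivity and PPV. Under the assumed 60% sensitivity, 90% specificity and 2% prevalence, result-driven labelling of 2-10% of false positives gives sensitivity 0.64-0.73 and PPV 0.13-0.20 in place of 0.11. The relabelling share is an assumption; nothing in the article fixes it. Specificity reaches at most 0.909, so a claim that it is materially inflated would not be supported. Neither would a claim that the estimates are known to be biased, or that the comparison between arms is biased in a known direction.

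**What to change.** 1. **Mask the assessment.** The two assessors and the panel set the diagnosis from the patient record with practice and arm identifiers removed. They have no access to the laboratory result forms, in particular the withheld supplementary results, until the diagnosis is locked. Keep two independent readings per patient.
2. **Flag and test.** Mark diagnoses that rest solely on a study blood test, and run a sensitivity analysis that does not count them as reference-positive. State that it may bias sensitivity downward, because some are true cases.
3. **Separate reporting.** Give per-test accuracy separately where the result was fed back and where it was withheld. Note that GPs choose which tests to order, so the two sets of patients are not exchangeable.

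A reading stripped of all T0 and T1 results should not become the primary one, since it would turn some true cases into reference-negatives. Masking is therefore partial: a dated result in the notes may still reveal the arm, and work-up already driven by a result cannot be undone. Items 2 and 3 expose what item 1 cannot remove.

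The cost is some redaction time, by someone other than the patient's assessors, and the additional analyses. The Cooperation section says data collection has ended and cleaning and analysis are under way. Diagnoses not yet assigned can be handled this way directly; the report should say how any already assigned were reached.

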### Quality improvement strategy

#### Development of the strategy

Determinants of blood test ordering for unexplained complaints – both those relating to the GPs and those relating to the patients – have been identified previously.[11,23] Based on these determinants, a quality improvement strategy has been developed using a systematic procedure based on intervention mapping techniques.[15] The strategy has been pilot-tested, after which slight adjustments were made based on the pilot results.

#### Content of quality improvement strategy

For each GP in group 3, the strategy consists of two small-group meetings and one outreach visit by the researchers to their practice. Table 2 provides more details on the content of the strategy. The first group meeting is led by a GP experienced in medical diagnostic decision-making and a behavioural scientist experienced in teaching communication skills, while the second meeting is tutored only by the behavioural scientist. The outreach practice visit is made by one of the researchers. We have also developed patient education leaflets and diaries, to be handed out by the GPs, and a video message about watchful waiting, to be shown in the waiting room. All materials have been developed by the research team.

**Table 2 T2:** Elements of the quality improvement strategy

**Elements of strategy**	
Contents of programme	Small group meeting 1 Part 1: Interactive explanation of diagnostic value of diagnostic testing for unexplained complaints and effect of watchful waiting policy on diagnostic value. Part 2: Discussion of difficulties experienced in practice when dealing with patients presenting with unexplained complaints. Goal setting to change behaviour in GPs' own practice. Small group meeting 2 Part 1: Discussion about experiences with behaviour change. Searching for solutions to barriers that have arisen. Part 2: Practicing difficult situations by means of video vignettes. Setting new goals to change own behaviour. Practice visit Discussing individuals' barriers to change and providing suggestions to overcome these, based on stage of change. In between meetings, GPs get the opportunity to work on their goals to change their behaviour.

Materials	– Course book. – Leaflets for patients with information about unexplained complaints. – Diaries about complaints and food intake to hand out to patients to fill in and later discuss together. – Video message for the waiting room, explaining the use of watchful waiting.

#### Procedure

At the beginning of the trial, all GPs in group 3 are invited to the small group meetings, which are organised regionally, usually at the regional hospital. These meetings are held with an interval of approximately four weeks. After these meetings, an appointment is made for the practice visit, which takes place at least 3 months after the second group meeting. GPs are encouraged to prepare for the meetings by doing homework assignments.

#### Control group

GPs in group 2 are the control group for GPs in group 3. In order to ensure a maximum contrast, no strategy is offered to group 2.

### Measurements

All measurement instruments, measurement times and variables are summarised in table 3.

**Table 3 T3:** Instruments and variables.

**Instrument**	**Variables**	**Time points**					**Population**	**Method**
		**T0**	**T1**^#^	**T1.5**^#^	**T6**	**T12**		**- Provision** **- Person who completes questionnaire** **(- Comments)**

GPs' background data	Personal data	x					All GPs	- By mail
	Practice characteristics	x						- GP
	CME	x						
	Laboratory facilities available in practice	x						

Complaint registration form (for each individual type of complaint)	Symptoms	x	x				All patients	- Present in practice
	Signs	x	x					- GP
	Working hypothesis	x	x					
	Degree of unexplainedness	x	x					
	Degree of suspicion of serious pathology	x	x					
	Degree of insecurity of GP	x	x					
	Satisfaction of GP	x	x					

Patients' background data (included in patient questionnaire)	Date of birth	x	x	x	x	x	All patients	- Handed out by GP (T0, T1)
	Country of birth	x	x	x	x	x		- By mail (T1.5-T12)
	Sex	x	x	x	x	x		- Patient
	Marital status	x	x	x	x	x		
	Type of health insurance	x	x	x	x	x		
	Level of education	x	x	x	x	x		

Patient questionnaire	Intensity of complaints	x	x	x	x	x	All patients	- Handed out by GP (T0, T1)
	Course of complaints	x	x	x	x	x		- By mail (T1.5-T12)
	Satisfaction with care	x	x					- Patient
	Anxiety	x	x					
	Quality of life	x	x	x	x	x		
	- RAND 36							
	- Euroqol thermometer							
	Utilisation of health care	x	x	x	x	x		

Test ordering form	Quality of test ordering	x*	x*				All patients	- Present in practice
	Quantity of test ordering	x	x					- GP

Test result form	Test results	x*	x*				All patients	- Laboratory
								- Laboratory staff

Record examination form	Final diagnosis					x	All patients	- Practice/university
	Utilisation of health care					x		- Researcher
	Use of watchful waiting strategy					x		

		**Meeting 1**		**Meeting 2**		**Practice visit**		

Reports of small group meetings	Participation	x		x			All GPs in intervention group	- Meeting room
	Learning effects	x		x				- Researcher

Evaluation forms of small group meetings	Valuation of programme	x		x			All GPs in intervention group	- Meeting room
	Learning effects	x		x				- Researcher
	Suggestion for improvement	x		x				

GP interview in practice	Barriers and facilitators during change					x	All GPs in intervention group	- Practice
	Stages of change					x		- GP

Cost registration	Costs of development and organising of strategy	x		x		x		- University
								- Researcher

* T0 for patients randomised to group 1, T1 for all patients but only if they revisit their GP

^# ^T1 is the time point to measure a follow-up visit by the patient 4 weeks after inclusion. If a patient does not return to the GP, a questionnaire is sent by mail after 6 weeks. This time point is indicated as T1.5.

Most questions in the questionnaires have been formulated by the research team, based on topics found in the literature. Quality of life is measured by the RAND SF36, together with the thermometer of the Euroqol questionnaire. Both are widely used and have been validated extensively.[24-26]

#### Patients

Findings of history taking and physical examination are recorded on a prestructured complaint registration form by the GP after the consultation(s).

All patients are given the first questionnaire at the first consultation and a second questionnaire at the second consultation after 4 weeks. Patients who do not return to their GP after 4 weeks are sent a questionnaire by mail. Patients from all groups receive follow-up questionnaires by mail at 6 and 12 months after the initial consultation.

After 12 months, i.e. at the end of the follow-up period, data on the final diagnosis and health care consumption are collected from the patients' records by the researchers (MB and HK).

Copies of test ordering and result forms are collected by the researchers (MB and HK) from the regional laboratories.

#### GPs

Background data of all participating GPs are collected before the start of the patient inclusion process. Data on whether the GPs are satisfied with the consultation, whether they suspect serious pathology and whether they are certain about the diagnosis are collected from the complaint registration form. The GPs' test ordering behaviour is derived from the test ordering forms and the patient records. GPs in group 3 are asked to complete evaluation forms on process items of the quality improvement strategy. In addition, the determinants of their change processes they mentioned are audiotaped during the practice visit that is part of the quality improvement strategy.

### Data analysis

#### Primary outcome measures of the diagnostic intervention

The first primary outcome is the accuracy and added value of blood tests in detecting serious pathology (per test and in combinations relevant to general practice), related to and in addition to signs and symptoms. Serious pathology is defined as pathology requiring treatment. The second primary outcome is the effect of a 4-week postponement of test ordering on the blood test characteristics.

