### Objectives of the study

The first objective of the ongoing study presented here is to determine the accuracy of diagnostic blood tests or combinations of such tests and their value, in addition to signs, symptoms and contextual factors, for the purpose of discriminating between self-limiting diseases and serious pathology in patients presenting with unexplained complaints. The second objective is to compare the accuracy of a watchful waiting strategy with that of immediate test ordering. The third objective is to evaluate the effects of a systematically designed quality improvement strategy for GPs, aiming at the postponement of blood test ordering in patients with unexplained complaints.

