### Clustered randomised clinical trial

Participating general practices are randomised over 3 groups (figure 1). GPs in group 1 are instructed to order blood tests immediately at the first consultation. Those in group 2 are instructed to restrict blood test ordering to patients with complaints persisting after four weeks. GPs in group 3 are also instructed to try and postpone test ordering, but they also participate in a quality improvement strategy that supports them in postponing test ordering for patients with unexplained complaints. The study design includes two sub-studies. The first is a diagnostic study comparing patients from group 1 (immediate test ordering) with patients from groups 2 and 3 (4 weeks of watchful waiting). The second is a quality improvement study, comparing group 2 (instruction to postpone test ordering) with group 3 (instruction to postpone test ordering plus quality improvement strategy) in terms of the actual postponement of test ordering.

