### Procedure

If, after history taking and physical examination, a patient is considered to have unexplained complaints and gives informed consent, the GP enrols the patient in the study. Depending on the GP's study arm, blood test ordering or a 4-week watchful waiting policy is suggested to the patient. All patients are asked to return to the GP if complaints do not disappear within 4 weeks. If patients return, blood tests are ordered for every patient, irrespective of GPs' study arm. This means that patients in group 1 are then tested for the second time and patients in groups 2 and 3 for the first time.

All tests are performed at the regional laboratory, according to local standard operating procedures and using the local reference values.

Patient follow-up ends at 12 months after the initial consultation.

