#### Types of analysis

An intention-to-postpone analysis will be performed. Longitudinal comparisons will be made using repeated measurements techniques and multilevel analysis to correct for potential clustering of outcomes in GPs and practices. Barriers to and facilitators of change are analysed qualitatively.

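### Objective 2 asks how accurate watchful waiting is as a strategy, but the second primary outcome describes postponed tests only in patients who return, and no listed outcome counts pathology in those never tested

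*Protocol article*

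**What the plan says.** Under Objectives of the study, the protocol article states: "The second objective is to compare the accuracy of a watchful waiting strategy with that of immediate test ordering". Under Primary outcome measures of the diagnostic intervention, the corresponding item reads: "The second primary outcome is the effect of a 4-week postponement of test ordering on the blood test characteristics". The section on the clustered trial describes the diagnostic sub-study as group 1 patients against group 2 and 3 patients.

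The Procedure section says that patients who return at four weeks are tested whichever group they belong to: "This means that patients in group 1 are then tested for the second time and patients in groups 2 and 3 for the first time". In Table 3 the test-result row carries an asterisk, and its footnote reads: "T0 for patients randomised to group 1, T1 for all patients but only if they revisit their GP".

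Testing at inclusion is nevertheless possible in groups 2 and 3: "When watchful waiting is not considered feasible by the GP, e.g. because a patient insists on being tested, test ordering is allowed". The final diagnosis at 12 months is collected from the records of all patients. On analysis, the article says: "An intention-to-postpone analysis will be performed". It does not define that term further.

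**The concern.** The accuracy of a test and the accuracy of a strategy are different quantities. Test sensitivity is the share of tested patients with disease who have an abnormal result. The sensitivity of waiting also depends on whether a patient with disease comes back and is tested at all. Revisiting happens after randomisation and may depend on the arm, the complaint and the disease, so results in returners do not inherit the protection of randomisation.

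The Abstract's case for waiting is that it cuts testing and false positives without overlooking serious disease. The first half can be studied in test results. The second half depends on patients who waited, did not return and were later diagnosed. Neither the primary outcomes nor Table 4 contains a measure that counts them. Research question 3 addresses cost-effectiveness, but the items it names are costs, work absence, uncertainty, satisfaction and quality of life, not missed pathology. Followed as written, the plan could report good test characteristics after postponement and leave the second half of its premise unexamined.

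**Working it through.** **Figures from the article.** The Power calculation section gives 2% serious pathology and 100 cases needed. 100 / 0.02 = 5000, which reproduces the stated total. A third of this is 5000 / 3 = 1667 per group (stated as about 1700). Expected cases are 1667 × 0.02 ≈ 33 in group 1 and 3333 × 0.02 ≈ 67 in groups 2 and 3 together.

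**Who has an index-test result under the Table 3 footnote.**
- Group 1: everyone at T0, and returners again at T1.
- Groups 2 and 3: returners at T1. Early-tested patients have no scheduled T0 result.
- Groups 2 and 3, never tested: no result, but a 12-month diagnosis.

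**Illustration.** These inputs are assumed and are not in the article: test sensitivity 0.70 and specificity 0.85, both the same at T0 and T1 and unrelated to return; no early testing in groups 2 and 3; 80% of cases and 40% of non-cases return. Prevalence is the article's 2%.

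- Strategy sensitivity = test sensitivity × share of cases returning. At 60%, 80% and 90% return this is 0.42, 0.56 and 0.63. Sensitivity among returners is 0.70 throughout.
- Missed cases per 1000 = 20 × (1 − sensitivity). Immediate testing: 20 × 0.30 = 6.0. Waiting: 20 × 0.44 = 8.8 at 80% return, 11.6 at 60% and 7.4 at 90%.
- False positives per 1000. Immediate testing: 980 × 0.15 = 147. Waiting: 980 × 0.40 × 0.15 ≈ 59.
- Positive predictive value. Immediate testing: 0.014 / (0.014 + 0.147) = 0.087. Returners: 0.0112 / (0.0112 + 0.0588) = 0.16.
- Cases without a T1 test among the 67: about 27 at 60% return and about 7 at 90%.

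With an assumed test sensitivity of 0.80, strategy sensitivity runs from 0.40 at 50% return of cases to 0.80 at 100%, while the returner figure stays at 0.80. Only complete return of cases closes the gap.

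**Early testing.** The share is not stated. If 10% to 30% of the 3333 patients in groups 2 and 3 were tested at inclusion, that is 333 to 1000 patients and, at 2%, about 7 to 20 cases.

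**Which tests to count.** If any abnormal test up to the four-week visit counted as positive, group 1 returners would have two chances and group 2 and 3 returners usually one. With the same inputs and independent repeat errors, group 1 sensitivity becomes 0.70 + 0.30 × 0.80 × 0.70 = 0.87, and false positives become 980 × (0.15 + 0.40 × 0.85 × 0.15) = 197 per 1000. With perfectly correlated errors the values stay at 0.70 and 147. Using the first test only avoids this dependence.

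**Precision.** Before any allowance for clustering, the 95% half-width for a sensitivity of 0.70 on 33.3 cases is 1.96 × √(0.70 × 0.30 / 33.3) ≈ 0.16. For 0.56 on 66.7 cases it is 1.96 × √(0.56 × 0.44 / 66.7) ≈ 0.12. The strategy comparison would be imprecise and should be read through its intervals.

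**The case against.** The strongest reply is that the article is condensed and fixes no analysis set for this outcome. A reader might infer that all of group 1 at T0 will be compared with only the returners of groups 2 and 3. That contrast is reconstructed from the footnote and is nowhere stated. Because group 1 returners are retested, a comparison at T1 in both arms, or within group 1, is also possible. This stands. Those alternatives do not remove the difficulty, though: any use of T1 results conditions on return.

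A reader might also infer that early tests in groups 2 and 3 go unrecorded. They do not. On reasons, the article says: "In that case, the GPs are asked to state the reasons for not postponing test ordering on a special form". Table 3 records the quantity of ordering at T0 for all patients, ordering behaviour is also taken from patient records, and laboratory order and result forms are copied without restriction by arm. What is unclear is whether the T0 results of these patients are used, and whether the laboratory supplemented their tests to the full complaint-specific set, which is described only for group 1.

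Nor does the article state that missed cases are to be dropped. The 12-month diagnosis is collected for everyone, and an intention-to-postpone analysis could be read as including them. It is a possible reading, but no listed outcome makes it concrete.

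Finally, selecting patients with persistent complaints is the declared purpose of waiting, so a higher predictive value in returners is the hypothesis and not an artefact. That is right, and test characteristics in returners are worth reporting. They answer a different question from objective 2.

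**Conclusion.** The point holds as a mismatch between two stated items: the objective concerns a strategy, while the outcome concerns test characteristics that after postponement exist only in patients who revisit. Never-tested patients with pathology in groups 2 and 3 fall outside any test-sensitivity denominator and are counted by no listed outcome. Test characteristics alone therefore cannot show whether waiting misses serious pathology.

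How much this matters cannot be fixed from the article, which gives no return rate. The 42% to 63% against 70% rests on assumed test accuracy and return, and on sensitivity at four weeks equalling that at inclusion; only the 2% prevalence is the article's own. The documents do not support the claims that a biased contrast has been prespecified, that early tests are lost, or that missed cases are excluded by rule. This is a worthwhile, low-cost correction to make before results are reported.

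**What to change.** Keep the test characteristics in returners and label them as conditional on return. Alongside them, report strategy-level accuracy for objective 2 over all enrolled patients by assigned group:

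- Index result: the first study test, meaning T0 in group 1 and the first test up to the four-week visit in groups 2 and 3, early tests included.
- Never-tested patients: counted as strategy-negative.
- Reference: the 12-month diagnosis in every patient.
- Report: sensitivity, false positives per 1000 and missed cases per 1000, with cluster-adjusted confidence intervals.

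State that this is what the intention-to-postpone analysis means for objective 2. Reconcile the Table 3 footnote with the sections on watchful waiting and on patient measurements, so that T0 results of early-tested patients in groups 2 and 3 are taken from the laboratory copies already collected.

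The cost is modest extra analysis and data entry. The article says that data collection ended on 31 December 2004 and that cleaning and analysis are under way, so the addition must be declared as made after that date. Early-tested patients in groups 2 and 3 may lack the full supplemented test set. Their number, and the tests available for them, should be reported.
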